**Fig. 2 Fig2:**
[figure not shown]
Inclusion of patients and data collection (EMR = electronic medical records)

#### Intervention group

In the intervention group, the participant then receives a tablet with the app installed. The participant completes the digital medical history in the waiting area. At the end of the survey, the app generates a report from the participants’ responses, which is subsequently transferred to the EMR via a scanned QR-code. This report is available to the physician before the consultation. No data remains stored on the device itself.

When they are next in line, the participant goes to the doctor’s office for consultation. After the consultation, both the participant and the physician are asked to fill out a short questionnaire. The participant will be asked questions about their satisfaction with the consultation (EUROPEP) and about communication (PSQ) and socio-demographic questions. These questions will be presented on the study tablets using the survey software Limesurvey. Subsequently, each participating patient receives a compensation of EUR 15.

The physician is asked to document the ICD-10-GM code (WHO Version 2019) of the (preliminary) diagnosis, to answer questions about their experience of uncertainty regarding this diagnosis and questions matching those that the participant is asked about communication. Additionally, we will collect data regarding the physicians’ specializations and experience (i.e. year of approbation and year of the first specialist examination).

After 14 to 21 days, we conduct a short follow-up to ask participants about their further treatment (e.g. by their family doctor, specialist treatment and hospital admissions). Participants may answer these questions via an online questionnaire (accessed using a personalized link which is sent per e-mail or text message) or by telephone (interview conducted by a study nurse).

#### Control group

After approving consent and data protection declaration, participants of the control group transition to their medical consultation and will use the app for medical history after the encounter. Information gathered from the app is not transferred to the EMR. Therefore, contrary to interventional group, for control participants, physicians do not have additional information collected by the app. After the consultation, the participant and the physician are asked to complete questionnaires as described for the intervention group. Remuneration and follow-up procedure are then identical to the intervention group.

### Data management

Once transferred to the EMR, the information on the participants’ medical history collected by the app is available to the practice staff and this data is linked to the patient file. Pseudomized app data and questionnaire data are available to the project partners. The paper-based declarations of consent and the confirmation of receipt of the expense allowance containing personal information cannot be linked to this data. The contact details (telephone number and/or e-mail) are recorded together with the ID but stored separately from the consent forms and destroyed after expiration of the agreed time period of 21 days. Then, the data can no longer be traced back to study participants. Collected data is treated confidentially. The research team is aware of data privacy regulations and committed to data protection. Data and information are not shared with other authorities or third parties. Data evaluation and publication of results is exclusively anonymous. All study data will be destroyed or deleted 10 years after the end of the study.

### Sample size estimation

The sample size is driven by the primary outcome diagnostic accuracy. For the planning of the study, we assume the diagnostic accuracy will increase by 10% points, with an expected current diagnostic accuracy of 70–80% [4, 27]. In a design with randomization of individual participants, a case number of 335 participants per group (670 participants in total) gives a power of 90% at a two-sided significance level of 5% assuming diagnostic accuracies of 75% and 85% in the control and intervention groups, respectively.

To correct for the randomization of clusters (time periods), the number of cases is multiplied by the design effect. The design effect is a function of the size of the clusters and the correlation within the clusters (ICC). We originally assume a cluster size of 36 participants per cluster of two weeks in both practices overall and an ICC of 0.01. The difference between the two practices is accounted in the analysis model by a fixed-effect co-factor. This results in a design effect of 1.35. In addition, we count for about 5% drop-out of the participants. This results in a rounded total number of cases of n = 1,000. In the execution of the study, we reduced the duration of each cluster to one week and thereby increased the number of clusters from 26 to 52. This reduced the number of cases needed (originally 952) slightly to 825. This adjustment does not reduce the power of the study and is determined to be convenient in its implementation. The duration of the study is kept at 12 months to cover all seasons.

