### Study design

To evaluate the effect of the developed app, a two-center, open-label, cluster-randomized trial (CRT) time-periods as clusters and groups under intervention or control condition will be conducted. In the intervention group, patients use the developed app in the waiting area before the encounter and the obtained information is available for the medical assistants and physicians before the consultation. In the control group, patients use the app after the consultation. The entered information is thus not available before the encounter. Clusters are defined as time periods of one week. In each week one practice is in the intervention group, the other one in the control group. The randomization of control and intervention group takes place before the start of the study in blocks of two weeks (see Fig. 1). Due to the two-weeks-block randomization, it is possible that a practice is in the control or intervention group for a maximum of two consecutive weeks.

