#### Big Data objectives

At the time of the final evaluation, there is an extensive standardized dataset of approximately 1,000 patients. A partial data set is to be evaluated in the context of a machine learning / data mining procedure. The aim is (a) to assess the usability of the data for further purposes (intelligent patient management and diagnostics) and to demonstrate this in a use case (e.g. predicting hospital admission), and (b) to characterize the usage process and to identify possibilities for improvement of the user interface.

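### The design effect is applied to a time period that contains both arms, so 825 is not the number that gives 90% power in the design described (conservative at the stated ICC)

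*Protocol article*

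**What the plan says.** Protocol article, Sample size estimation: 335 participants per group give 90% power at a two-sided 5% level, "assuming diagnostic accuracies of 75% and 85% in the control and intervention groups, respectively". For clustering, "We originally assume a cluster size of 36 participants per cluster of two weeks in both practices overall and an ICC of 0.01". "This results in a design effect of 1.35", and with 5% drop-out the total is rounded to 1,000. The cluster length was later cut to one week, which raised the number of clusters from 26 to 52: "This reduced the number of cases needed (originally 952) slightly to 825". The 12-month duration was kept.

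Protocol article, Study design: a cluster is a period of one week, and "In each week one practice is in the intervention group, the other one in the control group". Allocation is randomised in blocks of two weeks.

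Protocol article, Statistical design: the primary model has group and practice as fixed effects and the time period, labelled as the cluster, as the random effect.

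Protocol article, Big Data objectives: at the final evaluation "there is an extensive standardized dataset of approximately 1,000 patients".

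**The concern.** The factor 1+(m−1)ICC describes how much variance an arm mean gains when m correlated people all sit in that arm. The cluster in the sample size section is a period counted over both practices. Because the practices are always in opposite arms, about half of its members are in each arm. A correlation shared by the whole period then largely cancels from the arm contrast instead of inflating its variance. The unit that does carry one arm, a practice in a given week, is about half the size used.

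Two things are at stake. The required number and the power printed beside it do not belong to the design described. And the ICC, the least certain input, is attached to a unit that does not drive the variance, so a reader cannot judge how much margin the trial has. The same ambiguity reaches the primary model: the text does not settle whether the random effect is the calendar week or the practice-week.

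**Working it through.** **Inputs from the protocol article.** Rates 75% and 85%, two-sided α 0.05, power 90%, ICC 0.01, 36 participants per two weeks over both practices, drop-out 5%, 52 weeks, practices in opposite arms each week.

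**Step 1: reproduce the plan.**
- Individually randomised size per arm: [1.96·√(2·0.80·0.20) + 1.2816·√(0.75·0.25 + 0.85·0.15)]² / 0.10² = 334.2, rounded up to 335, so 670 in total.
- Two-week period, both practices, m = 36: design effect 1 + 35·0.01 = 1.35; 670·1.35/0.95 = 952.1.
- One-week period, both practices, m = 18: design effect 1 + 17·0.01 = 1.17; 670·1.17/0.95 = 825.2.

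The arithmetic is right. Both totals match, which shows that the cluster sizes used were the ones pooled over the two practices.

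**Step 2: apply the calculation to units that fit the design.**

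| Unit | m | Factor | Required N |
|---|---|---|---|
| Practice-week, one arm | 18/2 = 9 (assumes equal volumes) | 1 + 8·0.01 = 1.08 | 670·1.08/0.95 = 762 |
| Calendar week shared by both arms | contrast lies within the week | about 1 − 0.01 = 0.99 | 670·0.99/0.95 = 698 |

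Neither gives 825.

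On unequal volumes: the listed regular opening hours are about 54 and 36 a week. If participants split in that ratio (10.8 and 7.2), the weighted mean size is (10.8² + 7.2²)/18 = 9.36 and the requirement is 670·1.0836/0.95 = 764. The equal-volume assumption hardly matters.

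**Step 3: power at 825 enrolled.** The effective size per arm is 825·0.95/(2·factor).
- Factor 1.17 (as planned): 334.9 per arm, power 90.1%.
- Factor 1.08 (practice-week): 362.8 per arm, power 92.2%.
- Factor 0.99 (shared week): 395.8 per arm, power 94.2%.

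**Step 4: dependence on the practice-week ICC, which the article does not give.** With m = 9, the required N is 733 at ICC 0.005, 762 at 0.01, 818 at 0.02 and 987 at 0.05.

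Nine per practice-week over 104 practice-weeks is 936, which equals 52·18 and 26·36. At 936 enrolled with 5% drop-out:
- ICC 0.01: 936·0.95/(2·1.08) = 411.7 per arm, power about 95%.
- ICC 0.05: factor 1.40, 317.6 per arm, power 88.5%. If the cluster size is also reduced for drop-out (8.55), the factor is 1.3775 and power is 89.0%.
- Power of 90% is kept up to an ICC of about (936·0.95/670 − 1)/8 = 0.041.

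**The case against.** The strongest reply is that the error costs nothing at the stated ICC. The plan asks for more participants than either workable reading needs, and its statement that the shorter clusters do not reduce power is true. That stands, and it limits the weight of the point.

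The figures 1.35 and 952 are presented as the original plan, whose allocation is not separately described. They would have been right if both practices had then shared an arm in each period. The article reports only a change of cluster length, so this cannot be settled. The point therefore rests on 825.

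The replacement figure of 762 is not fixed by the document either: it transfers an ICC stated for a pooled period to a different unit. That also stands, which is why a range is needed.

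Three stronger readings are tempting, and the documents do not support them:
- **That 104 units are randomised rather than 52.** One practice's arm fixes the other's, and allocation is drawn in two-week blocks. The 104 practice-weeks are single-arm cells, not independent randomisations.
- **That 825 and about 1,000 contradict each other.** The first is a number needed. The second describes an expected dataset after a fixed 12 months, and the assumed rate gives 936. Only a linking sentence is lacking.
- **That power falls to about 84% at ICC 0.05 and 74% at ICC 0.10.** Those values pair 9 per practice-week with 825 participants, whereas 9 per practice-week implies 936.

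**Conclusion.** The concern holds as a fault in the unit of clustering, not in the arithmetic. The design effect is computed for a period that always contains both arms, and no reading of the current design gives 825 at ICC 0.01. The requirement is about 762 on practice-weeks or about 698 if the correlation belongs to a week shared by both arms, and power at 825 is about 92% or 94% respectively, not 90%. The practice-week figures assume about equal practice volumes and an ICC of 0.01 at that level.

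A reader might infer that the trial is underpowered. At the stated ICC it is not. On practice-weeks 825 falls short only if the ICC is slightly above 0.02, and the expected 936 only above about 0.04. The point is worth correcting because the printed power and margin are not those of the trial described, and because the same unclear cluster label carries into the primary model.

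**What to change.** In the sample size section, restate the calculation on the single-arm practice-week: 104 practice-week cells (described as cells, not as 104 independent randomisations), about 9 participants each, and the ICC that belongs to that unit with the reason for its value. In the statistical design section, say whether the random effect is the week or the practice-week, and align it with the unit used for the sample size.

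Give the power at the expected 12-month enrolment of 936 over a range of ICCs: on the present assumptions about 95% at ICC 0.01 and about 88–89% at ICC 0.05, after 5% drop-out. Add one sentence on how the number required relates to the 936 to 1,000 expected.

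The cost is text only, with no change in recruitment. The one drawback is that the restated power depends on a practice-week ICC that the article does not give, so it has to be shown as a range, not as a single figure.

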### Statistical design

We will use descriptive statistics to analyze patient characteristics (i.e. demographics, medical complaints) of intervention and control group. Furthermore, the groups will be compared according to characteristics of the recruitment centers.

The primary outcome “diagnostic accuracy” defines the agreement of a given diagnosis with the determined correct diagnosis. The primary evaluations of the binary endpoint of an adequate diagnosis are performed by a generalized linear mixed-effects model (hierarchical or multilevel model) with logit link function. The group (intervention versus control) and the respective out-of-hours practice are included as fixed effects, and the time period (cluster) as a random effect. The random effect is assumed to be normally distributed on the logit scale. The expected value is 0. The variance is unknown and estimated from the data. The odds ratio for the intervention effect will be reported together with its 95% confidence interval and a p-value for the null hypothesis that the intervention does not increase the diagnostic accuracy. Subgroup analyses will explore whether practice characteristics such as experience or specialization of the physicians have an influence on the strength of the intervention effect. This will be done by extending the model described above. Specifically, the respective practice characteristic as well as its interaction with the intervention effect will be included in the hierarchical model. With regard to the secondary endpoints, the individual items of the respective questionnaires are first presented within the framework of descriptive statistics (median, max, min, percentiles). Differences between the intervention and control group are analyzed for each item of the questionnaires using non-parametric methods. Except for the primary endpoints all endpoints are considered exploratory. Therefore, p-values will not be adjusted for multiplicity. Further explorative evaluations will be conducted using machine learning and data mining procedures: methods that are known to work well with a medium sample size will be used for classifications. These methods should have the potential to capture the structure of the underlying associations. We assume that some effects of inquired symptoms on the suspicion of disease severity are additive and individually assessable while others are more likely to conform to a relation like “at least k of n criteria have to be met and none of the following contra-indications” and are more specific to single diseases. We use elastic nets for classifications, because they perform well with the first class of symptom effects even when the number of inquired symptoms is larger than the number of patients. We will also use random forests, because they structurally have some similarity to decision tree like associations that can handle the second class of symptoms. We will utilize the results from these methods to artificially expand the data set for (or to pre-train) more flexible algorithms, such as support vector machines and artificial neural networks. These will then be used to search for more complicated associations. Medical history information, demographic information, treatment information (e.g. diagnosis, examination findings), and event-sourcing information (tracking of the app-usage of individual patients, e.g. time needed to complete) will be used as input variables. In addition, cluster, association and regression analyses will be performed. Results will be visualized and interpreted. Test data from the overall evaluation will be used to determine sensitivity, specificity, and accuracy of prediction models.

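### The primary null hypothesis is worded one-sidedly, which does not match the two-sided 5% level behind the sample size or the 95% confidence interval reported beside it

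*Protocol article*

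**What the plan says.** In the protocol article, Statistical design, the primary endpoint is analysed with a logistic mixed model. Group and practice are fixed effects and time period is a random effect. The group effect is to be given as an odds ratio with a 95% confidence interval and "a p-value for the null hypothesis that the intervention does not increase the diagnostic accuracy". The section neither calls the test one-sided nor gives a threshold for this p-value. It treats every endpoint other than the primary as exploratory.

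Under Sample size estimation, the calculation for individual randomisation "gives a power of 90% at a two-sided significance level of 5" per cent, "assuming diagnostic accuracies of 75% and 85% in the control and intervention groups, respectively". This is the only significance level in the article.

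**The concern.** A null that says accuracy is not raised covers both no effect and harm: odds ratio at or below 1. The matching p-value is one-sided. A two-sided test has the null odds ratio = 1. The two sections therefore describe different tests for the single confirmatory comparison. This is not a detail left to a later document, because the article states the null and states the level, and the two do not fit together.

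When the estimate favours the app, the one-sided p-value is half the two-sided one. An analyst who follows the Statistical design wording and looks for a threshold finds only 5%. Used that way, the trial could be declared positive on a result whose 95% interval includes 1, and the article does not say which of the two would decide. The trial is open-label and its authors expect improvement, so the decision rule should not be open to choice once data are seen.

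**Working it through.** **Inputs** (Sample size estimation): accuracy 75% in control and 85% in intervention; power 90%; two-sided 5%; 335 per group, 670 in total; ICC 0.01; cluster size 36; drop-out about 5%. The size of a one-week cluster is not stated; 18 is taken here as half of 36.

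**1. Reproduce the planned sample size.** Two proportions, pooled variance under the null, no continuity correction:

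n = [z(α)·√(2·p̄·(1−p̄)) + z(power)·√(p1(1−p1) + p2(1−p2))]² / (p2−p1)²

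Here p̄ = 0.80, so 2·0.80·0.20 = 0.32. Also 0.75·0.25 + 0.85·0.15 = 0.315, and z(power) = 1.2816.

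- Two-sided 5% (z = 1.960): (1.960·0.5657 + 1.2816·0.5612)² / 0.01 = 334.2, so 335 per group. This matches the article.
- One-sided 2.5% (same z = 1.960): also 335.
- One-sided 5% (z = 1.645): 272.2, so 273 per group. No match.

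The planning fits a two-sided 5% test or, equally, a one-sided 2.5% test. It does not fit a one-sided 5% test.

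**2. Carry it through to the totals.**

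- Two-week clusters: design effect 1 + (36−1)·0.01 = 1.35, then 670·1.35/0.95 = 952.1. The article gives 952.
- One-week clusters: design effect 1 + (18−1)·0.01 = 1.17, then 670·1.17/0.95 = 825.2. The article gives 825.

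Both totals rest on the 335 per group from step 1.

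**3. Compare the candidate decision rules.** The middle column is the upper normal tail beyond the critical value. Power is at 335 per group under individual randomisation.

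| Rule | Chance of falsely declaring benefit at odds ratio = 1 | Power at 335 per group |
|---|---|---|
| Two-sided p at 5% | 2.5% | 90.1% |
| One-sided p at 2.5% | 2.5% | 90.1% |
| One-sided p at 5% | 5.0% | 94.6% |

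Total type I error at no effect is 5% for the first and third rules. The third puts all of it on the benefit side.

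**4. Where the p-value and interval could disagree.** Under the third rule, benefit is declared for z above 1.645, while a two-sided 95% interval excludes 1 on the benefit side only for z above 1.96. In between they conflict. For example, z = 1.80 gives a one-sided p of 0.036 and a two-sided p of 0.072. The lower limit of the log odds ratio is then (1.80 − 1.96) = −0.16 standard errors, so the interval includes 1. Under the first two rules no such gap exists.

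**The case against.** The strongest reply is that the article never states a one-sided 5% test. For the benefit-side error to double, someone must compute a one-sided p-value and also judge it at 5%, although the only 5% in the text is labelled two-sided. The simpler reading is that the authors meant the ordinary two-sided p-value for the group coefficient and described the null loosely, in the direction of the effect they hope for. The 95% interval in the same sentence supports that. This part stands: the inflation is conditional on a choice that the document does not make.

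Three stronger inferences are tempting, and the documents do not support them.

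- *That the stated test doubles the false-positive rate.* It could, under the third rule in the table, but no threshold for the p-value is given.
- *That the sample size was planned for a different test.* One-sided 2.5% also gives 335 per group, so a directional null at that level is fully consistent with the planning. The figures 273 and 94.6% belong only to a one-sided 5% test.
- *That harm could not be seen.* A directional p-value cannot be small for harm, but the odds ratio and its 95% interval are reported in any case, and an interval wholly below 1 would show reduced accuracy.

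The absence of detailed testing rules from a journal article is no fault in itself, since an analysis plan may hold them. That does not remove the mismatch, because both the null and the level are stated and a reader has to set one aside to make sense of the other.

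**Conclusion.** The point holds as a consistency correction that should be made. The directional null in Statistical design conflicts with the two-sided 5% level in Sample size estimation and fits poorly with the 95% interval beside it, taking that interval as two-sided in the usual way.

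Its possible size is a benefit-side false-positive rate of 5% instead of 2.5%, with p-value and interval in conflict for z between 1.645 and 1.96. This rests on the null being taken literally and the resulting p-value being judged at 5%. If either condition fails, the error rate is as planned. It is not a demonstrated inflation of type I error, and the sample size needs no change.

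**What to change.** Restate the sentence in Statistical design as a two-sided test of H0: odds ratio = 1 at the 5% level, reported with the two-sided 95% confidence interval from the same mixed model. If a directional null is preferred, keep it and state a one-sided 2.5% level; for claiming benefit the two are equivalent. Any separate analysis plan should carry the same sentence, settled before the outcome data are examined.

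The cost is one sentence. The model, data collection, interval and sample size (335 per group before inflation; 952 or 825 in total) stay as they are.

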#### Secondary outcomes

Secondly, we hypothesize that the app reduces physicians’ perceived diagnostic uncertainty, increases patients’ satisfaction and the satisfaction with communication of both. Secondary outcomes of the clinical trial are therefore:

the patients’ overall satisfaction,the patients’ satisfaction with the communication with the physician,the physicians’ satisfaction with the communication with the patient, and.the physicians’ perceived diagnostic uncertainty.

This data will be obtained using questionnaires for both participants and physicians. Participants’ overall satisfaction with the consultation will be assessed using questions from the standardized and validated questionnaire European Project on Patient Evaluation of General Practice Care Questionnaire (EUROPEP) in German language. This instrument comprises short questions on the quality of primary care which participants rate on a five-point Likert scale ranging from “poor” to “excellent” [21, 22]. The questions focusing on the communication for both, participants and physicians, are based on the Patient Satisfaction Questionnaire (PSQ) [23–25]. Each item is a secondary endpoint that will be analyzed individually.

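### Median, range and percentiles are too coarse a summary for the five-point satisfaction items, and no effect measure is named beside them

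*Protocol article*

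**What the plan says.** The Secondary outcomes section states directional expectations: higher patient satisfaction, better communication as rated by both sides, and less diagnostic uncertainty for the physician. EUROPEP is described as "short questions on the quality of primary care which participants rate on a five-point Likert scale". The communication questions "are based on the Patient Satisfaction Questionnaire (PSQ"), with no scale given, and the scale of the uncertainty questions is not given either. On the unit of analysis the section says: "Each item is a secondary endpoint that will be analyzed individually".

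Under Statistical design, "the individual items of the respective questionnaires are first presented within the framework of descriptive statistics (median, max, min, percentiles"). Then: "Differences between the intervention and control group are analyzed for each item of the questionnaires using non-parametric methods". Neither the percentiles nor the methods are specified. For the primary outcome the same section is explicit: "The odds ratio for the intervention effect will be reported together with its 95% confidence interval and a p-value". It also states: "Except for the primary endpoints all endpoints are considered exploratory".

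**The concern.** Five ordered categories carry their information in the category shares. The median, quartiles, minimum and maximum keep little of that. If the relevant cut points fall inside one category in both arms, the summaries agree whatever happens to the shares. If a cut point is crossed, the summary moves by a full category. Neither outcome shows how large the shift was.

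At stake is whether the trial can answer its own secondary question. A result such as median 5 (range 1 to 5) in both arms with a small p-value is possible, and it would not tell a reader how much satisfaction changed. This would remain even if the test were adjusted for clustering.

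**Working it through.** **Sample size used.** The article gives no figure for the secondary items, so the check uses its recruitment target. For 75% against 85%, two-sided 5%, power 90%: n = [1.960·√(2·0.80·0.20) + 1.282·√(0.75·0.25 + 0.85·0.15)]² / 0.10² = (1.109 + 0.719)² / 0.01 ≈ 334.2, so 335 per group, as stated. One-week clusters of 18 (half of 36) with ICC 0.01 give a design effect of 1 + 17·0.01 = 1.17. Then 670·1.17 / 0.95 = 825.2, matching the stated 825, or about 412 per arm.

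**Assumptions.** All rating distributions below are assumed, because the article gives none. Ratings are treated as independent.

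**Why a quantile stays or jumps.** Apply a common odds ratio of 1.5 by dividing each cumulative odds by 1.5.
- Control 2/4/12/27/55% (ratings 1 to 5). The share at 4 or below goes from 45% to (0.45/0.55)/1.5 = 0.545, i.e. 35.3%. The share at 3 or below goes from 18% to 12.8%. In both arms P25 = 4, median = 5 and P75 = 5. The top rating rises from 55% to 64.7% and the summary does not move.
- Control 2/5/15/30/48%. The share at 4 or below goes from 52% to (0.52/0.48)/1.5 = 0.722, i.e. 41.9%. The median jumps from 4 to 5. The top rating rises from 48% to 58.1%.

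The odds ratio is the same and the gain in top ratings is about 10 points in both cases, yet the first summary shows nothing and the second a full category.

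**How often.** Simulated trials: 1,000 per row, odds ratio 1.5, 412 per arm, comparing minimum, quartiles and maximum, with a Mann-Whitney test.

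| Assumed control distribution, % | Top rating, % | Summaries identical | Identical and test significant |
|---|---|---|---|
| 2/4/12/27/55 | 55 → 64.7 | 97% | 79% |
| 28 at rating 5, 52 at rating 4 | 28 → 36.8 | 89% | not computed |
| 2/5/15/30/48 | 48 → 58.1 | 20% | 11% |
| 3/7/20/35/35 | 35 → 44.7 | 8% | 4% |
| 5/10/25/38/22 | 22 → 29.7 | 8% | 4% |
| 2/5/15/33/45 | 45 → 55.1 | 3% | 1% |

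A 2,000-trial run of the first row gave 97.5% identical, 82% significant and 80% both. With odds ratios of 1.3 and 1.8, agreement was 97.8% and 96.4%. Agreement is therefore driven by the distribution far more than by the effect size.

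**Choice of percentiles.** In the first row, adding P5, P10, P90 and P95 cut agreement to between 22% and 27% across runs. The reason is again a cut point: the share at 2 or below goes from 6% to (0.06/0.94)/1.5 = 0.0638/1.5 = 0.0426, i.e. 4.1%, so P5 jumps from 2 to 3.

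**One worked data set.** Control 2/5/13/52/28%, intervention 2/3/10/38/47%, 412 per arm. Minimum 1, P10 3, P25 4, median 4, P75 5, P90 5 and maximum 5 agree in both arms; P5 is 2 against 3. The rank test gives z = 5.16, p = 2.5×10⁻⁷; dividing by √1.17 leaves z = 4.77. The probability index (chance that an intervention rating exceeds a control rating, ties counted half) is 0.596. The Hodges-Lehmann shift is 0. The odds ratio for the top rating is (0.471/0.529)/(0.279/0.721) ≈ 2.3. Moving the control top rating from 28% to 24% (control 2/5/15/54/24%, intervention 2/3/8/40/47%) makes P75 differ, 4 against 5.

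**The case against.** Medians and percentiles with a rank method are a conventional treatment of ordinal data, and a condensed article may leave the test, estimator and table layout to an analysis plan that is not shown. Much of this stands. An unnamed effect measure would not be a finding by itself. The point rests on the summary that the article does fix, which an estimator named elsewhere would not make suitable.

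Three stronger readings are tempting, and the documents do not support them.
- A reader might infer that the planned outputs as a whole would present the arms as equal. They would not: the rank test flags the difference in the cases above, and only the descriptive part can miss it. Nor is identity typical, given the 3% to 97% spread and the open choice of percentiles.
- A reader might infer that the plan can deliver no effect size. The article speaks of non-parametric methods, not of a bare test, and such methods can give direction and a probability index. It names no estimator and rules none out. The summaries are also described as a first step, so additions are not excluded.
- A reader might extend the point to every questionnaire item. Five categories are documented for EUROPEP only. For the communication and uncertainty items the point holds only if they also have few categories.

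**Conclusion.** The concern holds as a minor point on the stated summary. For the five-point EUROPEP items, and any other item with few categories, median, range and percentiles show either no difference or a full category step, and neither conveys the size of a shift. Identical quartiles and extremes can coexist with a clear difference, as in the assumed example with top ratings of 28% against 47%. The frequency cannot be fixed from the article. The 96% to 98% agreement belongs to one illustrative distribution, and the range over the distributions tried is about 3% to 97%. These figures assume independent ratings and 412 per arm. The coarseness itself needs neither assumption. No effect measure is named for these items, in contrast to the primary outcome. Severity is low because the endpoints are exploratory and no confirmatory conclusion depends on them. Even so, with many unadjusted item-level p-values, estimates and intervals are what a reader can use.

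**What to change.** For each item, report the percentage in every response category by arm, in place of or beside the listed summaries. Add an ordinal effect measure with a 95% confidence interval: either a cumulative odds ratio from a proportional-odds mixed model or a probability index. Include group and practice and the same time-period cluster term as in the primary model. The difference in the percentage giving the top rating can be shown as a readable companion.

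The cost is analysis wording and somewhat longer tables; data collection, sample size and conduct do not change. The proportional-odds form is an added assumption to check. In the worked data set the cumulative odds ratios at the four cut points are 1.00, 1.48, 1.45 and 2.30, so it can fail. The probability index does not need it.
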